**Table 7: MAL-031 Follow-up (F/U) & Surveillance Periods**

| **Month** | **1** | | **2** | **3** | **4** | | | **5** | **6** | **7** | **8** | **9** | | **10** | **11** | **12** |
| --- | --- | --- | --- | --- | --- | --- | --- | --- | --- | --- | --- | --- | --- | --- | --- | --- |
| Study Day | 0-30 | | 31-60 | 61-90 | 91-120 | | | 121-150 | 151-180 | 181-210 | 211-240 | 241-270 | | 271-300 | 301-330 | 331-364 |
|  | V  V  V | | V  V  V | V  V  V |  | | |  |  |  |  |  | |  |  |  |
| F/U Period for Unsolicited AEs | | | | |  | |  |  |  |  |  | |  |  |  |
| F/U Period for SAEs | | | | | | | | | | |  | |  |  |  |
|  |  | |  |  | | Post-vacc Safety Surveillance Period for SAEs | | | | |  |  | |  |  |
|  |  | |  |  | | |  |  |  |  | Long-term F/U Period (for Malaria & Immunogenicity) | | | | |
|  |  | |  |  | | | Monthly Field Workers Visits | | | | | | | | |
|  |  | |  |  | | |  |  | Quarterly WRP Kombewa Clinic Visits | | | | | | |

V = 7 day F/U for Solicited AEs following each vaccination (All cohorts shown)

“Study days” presented for Cohort A only

## Detailed Description of Study Stages & Visits

This study will be performed according to the following procedures. Each cohort (A, B or C) will be scheduled independently as indicated here. For a day-by-day schedule for all cohorts see Section 17.2.5: Specific Daily Schedule of Events.

**Days –35 to -1** **Screening & Enrollment of Subjects**

***Visit 1***

- Written Informed Parental Consent
- Assignment of Subject Identification (SID) number
- Provision of medical history by subject’s parent
- Health assessment and history directed physical examination (includes physical examination of all major body systems: ENT, pulmonary, cardiovascular, musculoskeletal, central nervous, renal, gastrointestinal and skin). Abnormal findings will be recorded on source documents.
- Check of all inclusion and exclusion criteria.
- Check weight
- Collect 2 ml venous blood sample for measurement of:
- Complete blood count (CBC),
- Chemistry profiles (Creatinine, ALT)
- Provide each parent with SID card containing subject’s unique study number and parent/subject photograph. The photograph will be taken only of eligible subjects who agree to participate and have been consented. It may be taken on any day within this period prior to the first vaccination.

**Day 0 Vaccination 1 (Dose 1a, 1b, or 1c)**

***Visit 2***

Before vaccination:

- Check subject’s SID card to confirm identity
- Review screening laboratory test results
- Review inclusion/exclusion criteria and check of contraindications/precautions
- Randomization
- Record any parental or subject complaints, symptom-directed physical examination and examination of the immunization leg for any abnormalities
- Record vital signs (axillary temperature [must be <37.5C], blood pressure, pulse)
- Record baseline data for solicited general symptoms.
- Check weight
- Collect 2 ml of whole venous blood for the measurement of:
- CBC, creatinine, ALT
- Serum for anti-MSP-1 antibody titer (store at –50C)
- Confirm that the subject’s randomization number and SID number agree with label on syringe
- Administer study vaccine dose 1; record date and time of injection.

After vaccination:

- Observe for 60 minutes.
- Record blood pressure, pulse, axillary temperature (at start and end of 60 minute observation period)
- Record site of injection examination
- Record solicited and unsolicited AEs
- Instruct parent(s) to return with subject to WRP Kombewa Clinic immediately should subject manifest any sign or symptom perceived as serious.

**Days 1-3 Daily Post- vaccination 1 follow-up visits**

***Visit 3-5***

- Record vital signs (temperature, blood pressure, pulse)
- Examine site of injection
- Record solicited and unsolicited AEs
- Symptom-directed general physical examination
- Check concomitant medications

**Day 7  3 days Day 7 Post-vaccination 1 follow-up visit**

***Visit 6***

- Record vital signs (temperature, blood pressure, pulse)
- Examine site of injection
- Record solicited and unsolicited AEs (of previous 4 days)
- Complete physical examination
- Check concomitant medications

**Days 14  3 days Day 14 Post vaccination 1 follow-up visit**

***Visit 7***

- Record vital signs (temperature, blood pressure, pulse)
- Brief medical history
- History-directed physical examination
- Record any unsolicited adverse events occurring after the last vaccine dose.
- Check weight
- Check concomitant medications
- Collect 2 ml of blood for determination of:
- Serum for anti-MSP-1 antibodies (Store at  -50°C)
- CBC, creatinine, ALT

**Day 30  7 days Vaccination 2 (Dose 2a, 2b, or 2c)**

***Visit 8***

Before vaccination:

- Check of subject’s SID number to confirm identity
- History-directed physical examination and examination of the site of injection for any abnormalities
- Check contraindications/precautions
- Record vital signs (axillary temperature, blood pressure, pulse)
- Review medical history and record any unsolicited adverse events occurring since last visit.
- Record baseline data for solicited general symptoms
- Check weight
- Collect 2 ml of blood for measurement of:
- Serum for anti-MSP-1 antibodies (Store at  -50°C)
- CBC, ALT, creatinine
- Confirm that the subject’s randomization number and SID number agree with label on syringe
- Administer study vaccine dose 2, record date and time of injection.

After vaccination:

- Observe subject for at least 60 minutes following vaccination.
- Record blood pressure, pulse, and axillary temperature (at start and end of 60 minute observation period)***.***
- Record solicited and unsolicited AEs
- Examine site of injection
- Instruct parent(s) to return with subject to WRP Kombewa Clinic immediately should subject manifest any sign or symptom perceived as serious.

**Days 31-33  7 Daily Post-vaccination 2 follow-up visits**

***Visit 9-11***

- Record vital signs (axillary temperature, blood pressure, pulse)
- Examine site of injection
- Record solicited and unsolicited AEs
- Symptom-directed physical examination
- Check concomitant medications

**Day 37  7 Day 7 Post-vaccination 2 follow-up visit**

***Visit 12***

- Record vital signs (axillary temperature, blood pressure, pulse)
- Examine site of injection
- Record solicited and unsolicited AEs (of previous 4 days)
- Complete physical examination
- Check concomitant medications

**Day Visit 44  7 Day 14 Post-vaccination 2 follow-up visit**

***Visit 13***

- Record vital signs (temperature, blood pressure, pulse)
- Brief medical history
- History-directed physical examination
- Record any unsolicited adverse events occurring after the last vaccine dose
- Check weight
- Check concomitant medications
- Collect 2 ml of blood for determination of:
- Serum for anti-MSP-1 antibodies (Store at  -50°C)

- CBC, creatinine, ALT

**Day 60  7 days Vaccination 3 (Dose 3a, 3b, or 3c)**

***Visit 14***

Before vaccination:

- Check subject’s SID number to confirm identity
- History-directed physical examination
- Check contraindications/precautions
- Record vital signs (axillary temperature, blood pressure, pulse)
- Review medical history and record any unsolicited adverse events occurring since last visit.
- Record baseline data for solicited general symptoms
- Check weight
- Collect 2 ml of blood for measurement of:
- Serum for anti-MSP-1 antibodies (Store at  -50°C)
- CBC, ALT, creatinine
- Confirm that the subject’s randomization number and SID number agree with label on syringe
- Administer study vaccine Dose 3; record date and time of injection.

After vaccination:

- Observe subject for at least 60 minutes following vaccination
- Record blood pressure, pulse, and axillary temperature (at start and end of 60 minute observation period)
- Record solicited and unsolicited adverse events
- Examine site of injection
- Instruct parent(s) to return with subject to WRP Kombewa Clinic immediately should subject manifest any sign or symptom perceived as serious

**Days 61-63  7 Daily Post-vaccination 3 follow-up visits**

***Visit 15-17***

- Record vital signs (axillary temperature, blood pressure, pulse)
- Examine site of injection
- Record solicited and unsolicited AEs
- Symptom-directed physical examination
- Check concomitant medications

**Day 67  7 Day 7 Post-vaccination 3 follow-up visit**

***Visit 18***

- Record vital signs (axillary temperature, blood pressure, pulse)
- Examine site of injection
- Record solicited and unsolicited AEs (of previous 4 days)
- Complete physical examination
- Check concomitant medications

**Day 74  7 Day 14 Post-vaccination 3 follow-up**

***Visit 19***

- Record vital signs (temperature, blood pressure, pulse)
- Brief medical history
- History-directed physical examination
- Record any unsolicited adverse events occurring after the last vaccine dose
- Check weight
- Check concomitant medications
- Collect 2 ml of blood for determination of:
- Serum for anti-MSP-1 antibodies (Store at  -50°C)
- CBC, creatinine, ALT

**Day 90  10 Day 30 Post-vaccination 3 follow-up**

***Visit 20***

- Record vital signs (temperature, blood pressure, pulse)
- Brief medical history
- History-directed physical examination
- Record any unsolicited adverse events occurring after the last vaccine dose
- Check weight
- Check concomitant medications
- Collect 2 ml of blood for determination of:
- Serum for anti-MSP-1 antibodies (Store at  -50°C)
- CBC, creatinine, ALT

**Day 120  14 to Day 240  14 Post-vaccination Safety Surveillance Period for SAEs**

- Children will be followed for SAEs through Study day 240
- Beginning on Study day 120 (for Cohort A; appropriate subsequent days for Cohorts B and C), parents/subjects will be visited monthly  14 days by field workers to remind them of appointments and to confirm their location.
- Parents/subjects will continue to attend the WRP Kombewa Clinic whenever they are sick.

**Day 240  14 to 364  14 Long Term Follow-up Period**

*Visit 21-23*

- Beginning on Study day 180 (for Cohort A; appropriate subsequent days for Cohorts B and C), parents/subjects will be asked to return to the WRP Kombewa clinic every 3 months  14 days when 2 ml of blood will be obtained for hemoglobin and serum anti-MSP-1 antibody measurement and history directed physical. This quarterly visit will substitute for a monthly field worker visit.
- Passive follow-up for malaria will consist of visits to the WRP Kombewa Clinic whenever the subject is sick. During each visit the subject will be evaluated and a malaria smear will be done whenever symptomatic malaria is suspected based on criteria outlined in Section 8.3.1.

**Table 8: Intervals between Study Visits**

| **Interval** | **Size of interval** |
| --- | --- |
| ***(Visit 2Visit 6)*** | ***7 ± 3 days*** |
| ***(Visit 2Visit 7)*** | ***14 ± 3 days*** |
| ***(Visit 2Visit 8)*** | ***30 ± 7 days*** |
| ***(Visit 8Visit 12)*** | ***7 ± 3 days*** |
| ***(Visit 8Visit 13)*** | ***14 ± 3 days*** |
| ***(Visit 8Visit 14)*** | ***30 ± 7 days*** |
| ***(Visit 14Visit 18)*** | ***7 ± 3 days*** |
| ***(Visit 14Visit 19)*** | ***14 ± 3 days*** |
| ***(Visit 12Visit 20)*** | ***30 ± 7 days*** |

**Table 9: Schedulea** of Routine Subject Evaluations for Cohort A

| Visit | 1 | 2 | 3-5 | 6 | 7 | 8 | 9-11 | 12 | 13 | 14 | 15-17 | 18 | 19 | 20 | 21-23 |
| --- | --- | --- | --- | --- | --- | --- | --- | --- | --- | --- | --- | --- | --- | --- | --- |
| **Study Day** |  | **0** | **1-3** | **7** | **13** | **29** | **30,31,34** | **36** | **42** | **62** | **63-65** | **69** | **73** | **91** | **120-364** |
| Written Informed Parental Consent | x |  |  |  |  |  |  |  |  |  |  |  |  |  |  |
| Verification of Eligibility Criteria | x | x |  |  |  | x |  |  |  | x |  |  |  |  |  |
| Medical History | x | x |  |  |  | x |  |  |  | x |  |  |  | x |  |
| Physical Examination | x | x |  | x | x | x |  | x | x | x |  | x | x | x | x |
| Weight checks | x | x |  |  | x | x |  |  | x | x |  |  | x | x | x |
| CBCd | Xb | x**c** |  |  | x | x**c** |  |  | x | x**c** |  |  | x | x | x |
| Serum Chemistry (ALT, Cr) | Xb | x**c** |  |  | x | x**c** |  |  | x | x**c** |  |  | x | x |  |
| Serum for Antibody Responses |  | x**c** |  |  | x | x**c** |  |  | x | x**c** |  |  | x | x | x**e** |
| Vital Signs (T, BP, P) | x | x**f** | x | x | x | x**f** | x | x | x | x**f** | x | x | x | x |  |
| Study Vaccine Administration |  | x |  |  |  | x |  |  |  | x |  |  |  |  |  |
| Check contraindications/precautions |  | x |  |  |  | x |  |  |  | x |  |  |  |  |  |
| Assess Adverse Events**g** |  | x | x | x | x | x | x | x | x | x | x | x | x | x |  |
| Assess Serious Adverse Events**h** |  | x | x | x | x | x | x | x | x | x | x | x | x | x | x**h** |
| Concomitant Medications**i** |  | x | x | x | x | x | x | x | x | x | x | x | x | x |  |
| Interim History |  |  | x | x | x | x | x | x | x | x | x | x | x |  | x |
| Monthly field worker visits**j** |  |  |  |  |  |  |  |  |  |  |  |  |  |  | x |
| Quarterly WRP KC visits |  |  |  |  |  |  |  |  |  |  |  |  |  |  | x |
| Review of Health Status**k** |  |  |  |  |  |  |  |  |  |  |  |  |  |  | x |
| Scheduled blood volumes | 2 | 2 | 0 | 0 | 2 | 2 | 0 | 0 | 2 | 2 | 0 | 0 | 2 | 2 | 6 |
| **Cumulative** Blood Vol. (mL) | 2 | 4 | 4 |  | 6 | 8 | 8 |  | 10 | 12 | 12 |  | 14 | 16 | 22 |
| 1. Visit numbers & Study day numbers are the same (with slight variations for the latter) for all cohorts; Days/dates for doses 2 & 3 are for planning purposes & are provisional only. 2. Performed within 35 days prior to randomization. 3. Blood collected just before immunization. 4. Limited to Hgb, WBC, lymphocytes, platelets; Hgb determination every 3 mo from Study days 120 to 364. 5. Serum for MSP-1 antibodies collected every 3 mo from Study day 120 to 364 6. Pre-dose, post dose and 60 min after each dose. 7. Solicited symptoms collected for 4-days and on day 7 after each dose. Unsolicited AEs collected for 30 days after each dose. 8. SAEs collected from 1st injection (Study day 0) through 6 months (180 days) after the last injection (Study day 240). 9. Concomitant medications collected through 30 days after last dose of study vaccine. 10. Monthly field worker visits to check on status of subjects. 11. Record any new onset chronic or acute diseases or other medically significant conditions, unscheduled clinic visits, and any new treatments since previous scheduled study visit. | | | | | | | | | | | | | | | |

## Definition and Management of Symptomatic Malaria

### Definition of Symptomatic Malaria

Because the present study is a safety, not an efficacy, trial, there is no need for a formal case definition of malaria. However, in the event that a subject presents to the WRP Kombewa Clinic with fever, history of fever within 48 hours, or an illness which the attending doctor suspects may be due to malaria infection, a blood slide will be taken to confirm the diagnosis. All subjects with asexual parasitemia will be treated with antimalarials as below.

### Management of Symptomatic Malaria during the Study

At the present time, Kenyan Ministry of Health recommendations (40) for the first-line treatment for symptomatic malaria in children 1 to 4 years old remain 1/2 tablet once of sulfadoxine 500 mg/pyrimethamine 25 mg. However, the treatment of malaria will differ from the MoH *Guidelines* because, currently, parasite strains present in Kenya show significant resistance to both the *Guideline*’s first- and second-line drug options (41, 42). Therefore, artemether/lumefantrine (Coartem) will be used for treatment of children who acquire uncomplicated malaria during the study. This drug has been shown to be safe and effective in children in Africa (43). Artemether/lumefantrine will be ad-ministered as a 6 dose regimen over 48 hours in accordance with the scheme outlined in Table 10.

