**Table 10: Artemether/Lumefantrine (Coartem/Riatem) Dosing Schedule**

| **Body weight (Kg)** | **No. tablets* at 0, 8, 24, 36, 48 & 60 hrs** |
| --- | --- |
| 5 to 14.9 | 1 |
| 15 to 24.9 | 2 |
| 25 to 35 | 3 |

*Each tablet contains 20 mg of artemether and 120 mg of lumefantrine

In addition to artemether/lumefantrine, and in the unlikely event of treatment failure with that drug combination, the following regimen will also be available at the WRP KC as an alternative for the treatment of uncomplicated malaria:

- *Malarone* Pediatric Tablets (atovaquone 62.5 mg and proguanil Hcl 25 mg) dosed according to the body weight schedule presented in Table 11.

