### **Drugs to Treat Malaria**

*Coartem* (artemther/lumefantrine) will be the first line agent for the treatment of uncomplicated malaria. In addition, both *Malarone* Pediatric Tablets (atovaquone 62.5 mg and proguanil Hcl 25 mg) and oral and parenteral quinine will be available on site at the WRP Kombewa Clinic as alternatives. These drugs will be used in standard doses and regimens as described in Section 8.3.2.

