### Malaria Treatment During the Study

Medications available for the treatment of clinical malaria (see Section 8.3.2) will include oral Coartem, Malarone, and sulfadoxine/pyrimethamine. Oral and parenteral quinine will also be available.

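### Section 8.3.2 describes six artemether/lumefantrine doses over 48 hours while its own Table 10 runs to 60 hours, and Section 14.5.2 lists a malaria drug that Section 8.3.2 moves away from

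*Protocol*

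**What the plan says.** **Duration and schedule.** Section 8.3.2 (Management of Symptomatic Malaria during the Study) states that artemether/lumefantrine is given "as a 6 dose regimen over 48 hours in accordance with the scheme outlined in" Table 10. Table 10, in the same section, sets the number of tablets by body weight (1, 2 or 3 per dose) and gives the dose times as "at 0, 8, 24, 36, 48 & 60 hrs".

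**Drug list.** Section 8.3.2 reports that the Ministry of Health first-line recommendations for children aged 1 to 4 years "remain 1/2 tablet once of sulfadoxine 500 mg/pyrimethamine 25 mg". It then explains that study treatment will depart from the national guideline because "parasite strains present in Kenya show significant resistance to both the" guideline's first- and second-line options. It concludes: "Therefore, artemether/lumefantrine (Coartem) will be used for treatment of children who acquire uncomplicated malaria during the study". The rest of the section adds Malarone, oral quinine for children under 11 kg, and parenteral quinine for severe malaria.

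Section 10.8.2 (Drugs to Treat Malaria) makes Coartem first line. It adds that Malarone and "oral and parenteral quinine will be available on site at the WRP Kombewa Clinic as alternatives".

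Section 14.5.2 (Malaria Treatment During the Study) points the reader to Section 8.3.2 but says the available medications "will include oral Coartem, Malarone, and sulfadoxine/pyrimethamine". It adds quinine in a further sentence.

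**The concern.** The sentence in Section 8.3.2 relies on Table 10 and then gives a duration that Table 10 does not have. A clinician who takes the 48-hour figure as the length of the course has a reason to regard it as finished at the fifth dose. One who works down the table gives a sixth dose at 60 hours.

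The drug list raises the same kind of problem. Section 14.5.2 cites Section 8.3.2 as its source. The only sulfadoxine/pyrimethamine regimen there is the national one that the study says it will not follow.

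What is at stake is consistent care of children aged 12 to 47 months for an illness that the protocol expects to be common. Section 4.8 cites 83% parasite prevalence in 1 to 4 year olds in the district and intense transmission from April through August. Section 17.2.1 plans vaccinations from 28 April to 21 July 2003. Section 8.3.1 requires antimalarial treatment of every subject with asexual parasitemia. The conflicting text is therefore likely to be consulted often.

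**Working it through.** **1. The stated duration against Table 10**

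Inputs: the text gives 6 doses and 48 hours (Section 8.3.2). The dose times are 0, 8, 24, 36, 48 and 60 hours (Table 10).

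- Number of doses in the table: 6. This agrees with the text.
- Span = last time − first time = 60 − 0 = 60 hours. The text says 48. Excess = 60 − 48 = 12 hours.
- Intervals: 8, 16, 12, 12 and 12 hours, which sum to 60.
- Doses at or before 48 hours: 0, 8, 24, 36 and 48, so 5 of 6.

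The 48-hour figure cannot be reproduced. Keeping all six doses gives 60 hours, and stopping at 48 hours gives five doses. No reading of Table 10 gives six doses in 48 hours.

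In tablets, by the weight bands of Table 10:

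| Body weight (kg) | Tablets per dose | Total if stopped at 48 h (× 5) | Total for all six times (× 6) |
|---|---|---|---|
| 5 to 14.9 | 1 | 5 | 6 |
| 15 to 24.9 | 2 | 10 | 12 |
| 25 to 35 | 3 | 15 | 18 |

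**2. The drug lists side by side**

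| Drug | Section 8.3.2 | Section 10.8.2 | Section 14.5.2 |
|---|---|---|---|
| Artemether/lumefantrine (Coartem) | yes, drug of choice for uncomplicated malaria | yes, first line | yes |
| Malarone | yes, alternative | yes, alternative | yes |
| Quinine, oral and parenteral | yes | yes | yes |
| Sulfadoxine/pyrimethamine | named only as the national drug from which the study departs | not listed | yes, listed as available |

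Three of the four rows agree. In the fourth, Section 14.5.2 conflicts with the section it cites and with Section 10.8.2. No arithmetic applies here; the conflict is visible on reading.

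**The case against.** The strongest reply on the schedule is that the text does not set out a second regimen. It gives no dose times or tablet counts of its own, sends the reader to Table 10, and agrees with the table on six doses. Stopping at 48 hours would break the text's own dose count. On this view the 48-hour figure is one inconsistent phrase. This has force and narrows the point: it is not a case of two complete, competing schedules. The contradiction remains, because the sentence attributes to the table a duration that the table does not have.

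On the drug list, Section 14.5.2 is a short summary in the ethics chapter. It speaks of availability, gives no dose or line of treatment, and sends the reader to Section 8.3.2, where the choice of drug is plain. That also stands, and it lowers the chance of misuse. It does not explain why a drug that Section 8.3.2 sets aside for resistance is listed for the same purpose under a reference to that section.

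A reader might go further in three ways that the documents do not support.

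- *That sites will treat differently.* The Section 7.1 overview gives one study center with two satellite field stations. Sections 8.3.2 and 10.8.2 place the antimalarials at the Kombewa clinic, and courses are supervised by a physician or clinical officer. Any difference would be between clinicians or between children.
- *That a large share of the 135 children is affected.* Multiplying 135 by an assumed share treated for malaria counts children treated, not children treated differently. The documents give neither share. The 83% figure is parasite prevalence, whereas the smear that leads to treatment under Section 8.3.1 follows fever, recent fever or suspected illness.
- *That endpoints are distorted.* Section 8.3.2 makes the next vaccination depend on symptoms resolving within 3 days, fever is a solicited event, and hemoglobin is compared in the safety analysis. Even so, nothing in the protocol links a 12-hour difference in the last dose to recovery, hemoglobin or antibody. Allocation is randomized within each cohort and assessment is blinded, so no route to a difference between arms is shown.

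**Conclusion.** The point holds as two textual contradictions in current, operative treatment instructions. First, Section 8.3.2 states 48 hours for a course that spans 60 hours in Table 10. The difference is 12 hours, and one of the six doses lies outside the stated period. Second, Section 14.5.2 lists sulfadoxine/pyrimethamine, which Section 8.3.2 departs from and Section 10.8.2 does not offer.

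Both can be confirmed by reading and rest on no assumption. They amount to a patient-safety inconsistency that clinicians at the single center could read in different ways. How often that would happen cannot be derived from the documents, and no harm to a given number of children or effect on an endpoint is shown. No sample-size or error-rate figure depends on it. The correction is still worth making, because the text governs treatment of young children for a common illness and the change costs almost nothing.

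**What to change.** Before first dosing, the sponsor and investigators should:

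1. reconcile the duration stated in Section 8.3.2 with the six time points in Table 10, so that text and table describe one course;
2. reconcile the drug list in Section 14.5.2 with Sections 8.3.2 and 10.8.2, so that all three name the same drugs;
3. carry the agreed wording to every other place where malaria treatment is described.

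Which schedule and which drug list are right is a clinical decision for the sponsor and investigators, and this review does not state or propose one. The cost is two wording corrections, with no change to visits, sample size or analysis.
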